#### Assessments of Mental Deterioration

Case managers and blinded clinical staff will make monthly assessments of participants using the Clinical Global Impression Scale (CGI) [26], the Social and Occupational Functioning Assessment Scale (SOFAS) [6], and chart reviews.

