##### The 21-Item Depression Anxiety and Stress Scale

The 21-item Depression Anxiety and Stress Scale (DASS-21) [31] is a measure of depression, anxiety, and stress over the previous week. Respondents rate each item on a 4-point Likert scale, ranging from 0 (not at all) to 3 (almost always). The DASS-21 has high reliability, a factor structure consistent with its subscales, and high convergent validity with other measures of anxiety and depression [32]. This scale is administered at baseline and 6 months.

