#### Trial Administration

Data will be collected from the Embrace2 in a continuous and ongoing manner for all participants. Case management and treatment will continue as per usual in the community mental health services. Case managers of participants in the integrated unWIRED arm will receive training on how to use the mHealth device and dashboard to monitor a participant’s mental state. Research staff will monitor the extent to which there are data uploaded from the device based on the Empatica Research Portal. If unWIRED participants are observed to have minimal adherence over consecutive days, the research psychologist can contact each participant to determine the reason for the disconnection and attempt to restore the device. During the trial, the research psychologist may send EMA text messages to the unWIRED participants to determine stress levels and their responses will be visible on the Empatica Research Portal. EMA messages will be sent according to a schedule and can also be sent manually by the research psychologist. Physiological data from each unWIRED participant’s previous day will be displayed on the Splunk dashboard, showing their activity, rest, and EDA. A link to the dashboard will be provided to case managers so they can view the information on their work computer. Case managers will use the information from the dashboard to enhance their clinical decisions. Clinical staff and participants will be encouraged to discuss data recorded from the device during their meetings and to include this information in their collaborative care plan. Case managers will be provided with a basic manual for interpreting the dashboard; however, a clinical response will be left to their clinical judgement. Throughout the trial administration, clinical staff will be asked to report on their participant’s ongoing functioning and distress, as described in the Assessments of Mental Deterioration section. The research team can provide support to case managers as needed.

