### Power Calculations and Statistical Analysis

The primary outcome for this study is to compare changes in treatment-related outcomes before and after the intervention for participants enrolled in the integrated versus unintegrated conditions. There are currently no trials examining the augmentation of treatment with an mHealth device, so sample size estimations are made using general calculations. Assuming a moderately sized advantage of the integrated (ie, unWIRED) versus unintegrated device on outcomes (effect size=0.5, 80% power, and a 2-tailed α of .05), we will require 63 participants per group.

The RCT component generally compares measures of mental health, distress, and functioning between the conditions, adjusted for baseline scores. For example, this analysis may focus on an intent to treat using a hierarchical linear model (HLM) to test the differential effects of the two treatment conditions, because this method allows the number of observations to vary between participants and handles missing data by calculating estimates of trajectories using maximum likelihood estimation. Fixed effects could be tested for intervention condition and time of assessment. Random effects in the unstructured models provide an index of the relative effects of the treatments over time. Fixed effects parameters may be tested with the Wald test (*t* test, *P*<.05, 2-sided) and 95% confidence intervals. Analyses will focus on the primary outcomes (ie, CGI scores) and secondary outcomes (eg, APQ6, BASIS-24, DASS-21, PSQI, and AQoL-8D) between the unWIRED group and the active control group, with the main outcome points being at the 6-month follow-up relative to baseline. All results are based on estimated mean values derived from HLM analyses. The within-subjects analysis will be comprised of linear fixed effects models using physiological measurements (ie, sleep, activity, and EDA) to predict measures of mental health, distress, and functioning. Baseline variables may be used as covariates when analyzing individual and between-group differences (eg, age, illness severity, treatments, and personality differences). Thematic analysis [38] will be used to examine individual and group qualitative feedback regarding the acceptability of the mHealth device and the unWIRED intervention for participants and case managers; there will be approximately 10-20 participants in the patient and clinician groups.

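### The trajectory rationale for missing data does not hold for the four named secondary scales scheduled only at baseline and month 6; the monthly clinician ratings should inform their missing scores

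*Protocol article*

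**What the plan says.** Power Calculations and Statistical Analysis introduces the model tentatively: "For example, this analysis may focus on an intent to treat using a hierarchical linear model (HLM"). It gives as a reason that the method "handles missing data by calculating estimates of trajectories using maximum likelihood estimation". It then applies the model across the board: "All results are based on estimated mean values derived from HLM analyses". The main contrast is defined "with the main outcome points being at the 6-month follow-up relative to baseline", and the outcomes named beside the primary CGI are "secondary outcomes (eg, APQ6, BASIS-24, DASS-21, PSQI, and AQoL-8D").

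The schedules are in the Measurements section. For DASS-21: "This scale is administered at baseline and 6 months". BASIS-24, AQoL-8D and PSQI have the same two time points, as does WAI-SR, which is not in the named list. APQ6 also has a 3-month score. For the clinician ratings: "Case managers and blinded clinical staff will make monthly assessments of participants using the Clinical Global Impression Scale (CGI"), with SOFAS alongside. Chart Reviews says that these ratings are made mainly from electronic records.

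Two further statements bear on missing forms. Trial Conclusion asks participants who withdraw early to complete the questionnaires at that point. Trial Administration provides contact in one arm only: "If unWIRED participants are observed to have minimal adherence over consecutive days, the research psychologist can contact each participant".

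**The concern.** A likelihood model can borrow from a participant's intermediate scores when the last one is missing. With two scheduled waves there are none. A participant who returns no form after baseline is in effect predicted from arm and baseline alone, however far they have declined since.

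The trial studies deterioration, so it is plausible that people who become unwell return fewer final forms. The data that would show the decline, monthly CGI and SOFAS ratings drawn largely from charts, can exist without a returned form. The article does not bring them into the self-report models; the only covariates it mentions are baseline variables. At stake are the month-6 arm means of four named secondary outcomes and, if missingness differs between arms, the treatment differences on them.

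**Working it through.** **The plan's own figure.** The sample size is not in dispute. With effect size 0.5, 80% power and two-sided α of 0.05, n = 2(1.960 + 0.842)²/0.5² ≈ 62.8, so 63 per group, as stated. (The t-test version gives 63.8, and power 79.5% at 63.) The 0.5 serves below as a yardstick only.

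**Schedules against the rationale.**

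| Outcome | Scheduled scores | Post-baseline scores left if month 6 is missing |
|---|---|---|
| CGI, SOFAS | monthly | earlier monthly ratings |
| APQ6 | baseline, 3, 6 months | month 3 |
| DASS-21, BASIS-24, PSQI, AQoL-8D | baseline, 6 months | none, unless a form was completed at early withdrawal |

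**What likelihood recovers with two waves.** In simulated data (2,000 participants, 25% of month-6 scores missing), a maximum likelihood mixed model gave an arm effect of -0.4548 (SE 0.0447). Analysis of covariance on baseline in completers gave -0.4548 (SE 0.0448). For the arm difference, the participants without a month-6 score add practically nothing.

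**Size of the bias.** The article gives no dropout rate, so every rate and correlation here is an assumption. Scores are in SD units and higher is worse. The model is:

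- late CGI: c = 0.5·y0 + √0.75·e
- month-6 score: y6 = 0.5·y0 + √0.75·(r·e + √(1 − r²)·f), with r from 0.3 to 0.7
- any true effect is subtracted from both in the integrated arm
- logit P(y6 missing) = arm intercept + slope·c, with the intercept set to give the stated rate

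With a true effect of 0.50 and slope 1 in both arms (400,000 participants per scenario):

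| Missing, control v integrated | Baseline-only estimate, r = 0.3 / 0.5 / 0.7 | With late CGI as auxiliary |
|---|---|---|
| 30% v 30% | 0.500 / 0.499 / 0.503 | 0.500 / 0.500 / 0.501 |
| 30% v 15% | 0.468 / 0.452 / 0.435 | 0.497 / 0.498 / 0.500 |
| 30% v 10% | 0.458 / 0.438 / 0.412 | 0.496 / 0.500 / 0.498 |
| 15% v 30% | 0.522 / 0.546 / 0.566 | 0.493 / 0.500 / 0.500 |

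With 20-30% missing, the control-arm month-6 mean looks 0.04 to 0.14 SD too healthy, even when the contrast is unbiased. The contrast bias is the difference between the two arm-mean biases. For example, at r = 0.5 the control mean is off by 0.099 with 30% missing and 0.051 with 15%; 0.099 − 0.051 = 0.048 = 0.500 − 0.452.

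With no true effect, 30% v 10-15% missing and slopes of 0.5 to 1.5, the bias runs from 0.017 SD to about 0.11 SD. Equal rates alone do not guarantee safety: with 20% missing in both arms but slope 1 in control and 0 in integrated, the bias is 0.04 to 0.09 SD, and with slopes 1 and 0.5 it is 0.02 to 0.04 SD. With the same rate and slope in both arms it is about zero.

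**Against sampling error.** With 63 per arm, a baseline correlation of 0.5 and 30% v 10% missing, the adjusted difference has SE ≈ √0.75·√(1/44.1 + 1/56.7) = 0.17 SD. A bias of 0.02 to 0.11 SD is therefore roughly 0.1 to 0.6 of one standard error.

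**The case against.** **Scope.** The model wording is tentative, and auxiliary variables are commonly left to an analysis plan that is not shown. That stands: silence on auxiliary variables is not itself an error. What remains is a stated reason for the model, coupled with a statement that all results come from it, which does not fit four of the five secondary outcomes named.

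**Likelihood cannot handle these scores at all.** A reader might infer this, but it is too strong. The method is valid if missingness depends only on arm, baseline score and any covariates in the model, and the article allows baseline covariates.

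**The primary result is at risk.** A reader might infer this too. The documents do not support it: the CGI is rated monthly, mainly from charts, so the trajectory argument works there.

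**Early withdrawal.** Forms are requested at withdrawal, so some leavers will have a post-baseline score, and the simulations gave them none. This reduces the problem. It does not help for participants who simply do not respond, and the article does not say how an off-schedule form enters the model.

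**The control arm will lose more unwell participants.** It is tempting to conclude this from the one-sided adherence contact. That contact concerns wearing, charging and pairing the device, not questionnaires. Everyone is asked for the final forms in the same way, and everyone has a case manager. The integrated arm also carries the extra burden of stress prompts. The imbalance could go either way, and the bias with it.

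**Circularity.** The simulations let the CGI drive missingness and then adjust for it, so near-complete removal of bias is built in. That stands: the real gain depends on how well the monthly ratings capture why forms are missing. Case managers also rate and are unblinded (Randomization), which is a reason to prefer the blinded ratings.

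**Conclusion.** The point holds for DASS-21, BASIS-24, PSQI and AQoL-8D, and not for CGI, SOFAS or APQ6. For a two-wave scale with no post-baseline form there is no trajectory to estimate, and validity rests on missingness depending only on arm, baseline score and any baseline covariates.

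If missingness follows later decline, arm means are biased. The between-arm difference is biased only when the rate or pattern of missingness also differs by arm. The 0.02 to 0.11 SD found under the assumed rates is at most about a fifth of the planned 0.5 (0.11/0.5 = 0.22), and that effect size was not set for these scales specifically. The documents fix neither the rates nor the direction. This is a secondary-outcome matter of minor to moderate priority, worth acting on because the useful data are already being collected.

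**What to change.** In Power Calculations and Statistical Analysis:

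1. Limit the trajectory rationale to CGI, SOFAS and APQ6.
2. For the two-wave scales, state the missing-at-random assumption and estimate the baseline-adjusted month-6 difference with monthly CGI severity and SOFAS, preferably the blinded ratings, as auxiliary variables. Use either multiple imputation by arm or a joint likelihood model of the scale and the monthly ratings.
3. Include any early-withdrawal form at its actual time rather than as a month-6 score.

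The cost is analysis wording and modest programming, with no new data, visits or participants. The downside is a slightly more complex model, and bias is removed only to the extent that the monthly ratings capture the reasons for missingness.

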## Results

The study received scientific and ethical approval at Western Sydney Local Health District. It is due to start in October 2020 and conclude in October 2022.

## Discussion

This study will determine whether integrating an mHealth device into clinical care is useful and effective in managing severe mental illness in young adults in the community. We plan to test this approach in a frontline community mental health setting, where we can examine its feasibility, acceptability, and efficacy for patients and case managers. While previous studies use mHealth devices for participants to self-monitor, this is among the first to stream information to both a patient and the treating mental health team. We hypothesize that the device will identify periods of increased stress and risk of mental deterioration.

A strength of this design is that it examines both between- and within-subjects components. An RCT is a gold standard in determining treatment efficacy, and the within-subjects design can control for individual differences. This study also takes several types of measurements regarding evidence of mental deterioration, symptoms, and functioning. Potential limitations with this protocol should also be noted. This study intends on using participants with a variety of diagnoses, with varying severities, and with psychosocial difficulties. While this increases its ecological validity, the variation may make it more difficult to detect group differences. This limitation highlights the importance of controlling for relevant variables as well as studying within-subjects variation. Furthermore, even severely unwell patients are more often stable than deteriorating, providing fewer opportunities to test the efficacy of the unWIRED approach. Hence, examining process variables is important, as is the mixed methods approach employed in this study. Finally, the design incorporates several measures to detect an effect; however, this increases the likelihood of type I error.

While ambitious, this project’s clinical implications are potentially significant. Any treatment that improves collaboration and early intervention may have a far-reaching impact on the treatment of severe mental illness in the community. The intervention could allow clinicians to remotely and unobtrusively monitor severely unwell patients in the community and provide an effective means to augment treatment.

## Appendix

Multimedia Appendix 1 Randomized controlled trial measurements, measurement reporter, and time points.

Multimedia Appendix 2 Scientific approval and reviewer reports from the authors' institution.

## Abbreviations

ANZCTR: Australian New Zealand Clinical Trials Registry
APQ6: Activity and Participation Questionnaire
AQoL-8D: Assessment of Quality of Life-8 Dimension
BASIS-24: Behaviour and Symptom Identification Scale-24
BFI-10: 10-item Big Five Inventory
CGI: Clinical Global Impression Scale
CONSORT-EHEALTH: Consolidated Standards of Reporting Trials of Electronic and Mobile Health Applications and Online Telehealth
CSV: comma-separated values
DASS-21: 21-item Depression Anxiety and Stress Scale
DSMB: data safety monitoring board
EDA: electrodermal activity
EMA: ecological momentary assessment
ESE: Engineering Und Software-Entwicklung GmbH
HLM: hierarchical linear model
mHealth: mobile health
NSW: New South Wales
PSQI: Pittsburgh Sleep Quality Index
QR: Quick Response
RCT: randomized controlled trial
SOFAS: Social and Occupational Functioning Assessment Scale
WAI: Working Alliance Inventory
WAI-SR: Working Alliance Inventory–Short Form Revised
